### Randomization and blinding

Using SAS 9.3.1 software (SAS Institute Inc., Cary, NC, USA), selected cases will be distributed in a 1:1:1 ratio to generate a randomized grouping table. Envelopes for the randomized grouping table will be prepared; the envelopes used are opaque, numbered in order, and contain the randomized serial numbers for grouping. According to the randomized serial numbers, individuals will be distributed to the observation groups and control group.

Researchers in charge of data collection, data statistics, and data evaluation will be blinded from the group allocation. However, individuals being treated and the physicians will not be blinded from the group allocation due to the different interventions in this trial.

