### Outcomes

Therapeutic effect:VAS of nasal symptoms score [14]

The scale includes overall nasal symptoms and differentiated nasal symptoms. The highest score for each section is 10, representing a symptom that is unbearable; the lowest score for each section is 0, representing a symptom with no influence. VAS score is accurate to one decimal place. It is used to evaluate the influence of overall nasal symptoms and differentiated nasal symptoms over the past week.

Data will be collected before the start of treatment (the baseline assessment) and at the end of each week during the treatment and follow-up periods.2.Rhinoconjunctivitis Quality of Life Questionnaire score [15]

The Rhinoconjunctivitis Quality of Life Questionnaire (RQLQ) includes 24 questions in seven sections: activity, sleeping, symptoms unrelated to nose and eyes, actual problems, nasal symptoms, ocular symptoms, and emotion. The score for each question is divided into seven levels: 0 = no influence, 1 = almost no influence, 2 = some influence, 3 = moderate influence, 4 = bad influence, 5 = worse influence, 6 = worst influence. The score is calculated separately in each section and the total score of these seven sections is considered as the RQLQ score. The highest possible score is 144. The scale is used to evaluate the influence of rhinitis symptoms on patient quality of life.

Data will be collected before the start of treatment (the baseline assessment) and at the end of each week during the treatment and follow-up periods.

The experimental indexes are serum CRH, plasma ACTH, cortisol, serum IL-4, and IFN-γ.

Data will be collected before the start of treatment (the baseline assessment), at the end of treatment, and 4 weeks after the treatment.

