### Sample size

This study is exploratory research designed to investigate the mechanism of acupuncture treatment for AR patients. With reference to the first stage of the clinical trial in the national drug register published in 2005, also based on a preliminary study and other research findings, the required sample size is 90; taking into account a 20% drop-out rate, a total of 108 cases will be recruited. Dongzhimen Hospital and Beijing Chaoyang Hospital are each responsible for 50% of recruitment for the clinical study. Another 36 healthy volunteers will be recruited as the control group, for a total of 144 cases.

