### Statistical analysis

Data from this clinical trial will be analyzed using SPSS version 21.0 software (released 2012, IBM Corp., Armonk, NY, USA). Demographic (age, sex, course, family history, et al.) and clinical data will be used as the baseline assessment to compare the two groups. The main and second indexes of therapeutic effects will be measured as mean ± standard deviation. Differences before and after the treatment in each group will be compared by paired *t*-test. ANOVA will be used in the comparison between groups. Count data will be measured by constituent ratio while chi-square test or non-parametric test will be used in the comparison between groups. *P*<0.05 indicates the difference is statistically significant.

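### The three arms are compared by ANOVA with no baseline covariate named, although every outcome has a baseline; adjusting for it would gain precision at no cost in data

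*Protocol article*

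**What the plan says.** The Statistical analysis section of the protocol article sets the comparison of arms on continuous outcomes in one sentence: "ANOVA will be used in the comparison between groups". It gives baseline data two other uses. One is descriptive, where demographic and "clinical data will be used as the baseline assessment to compare the two groups". The other is within each arm: "Differences before and after the treatment in each group will be compared by paired" t-test. No covariate, hospital term or within-patient model is named for the comparison between arms. The significance rule is P"<0.05 indicates the difference is statistically significant".

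The Outcomes section shows what is available. VAS and RQLQ are recorded before treatment and then "at the end of each week during the treatment and follow-up periods". For the blood markers (CRH, ACTH, cortisol, IL-4, IFN-γ): "Data will be collected before the start of treatment (the baseline assessment), at the end of treatment, and 4 weeks after the treatment". The Trial design section gives 8 weeks of treatment and 4 of follow-up. Each scale therefore has a baseline and 8 + 4 = 12 later scores, and each marker has a baseline and two later values.

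Under Sample size, 90 patients are required and 108 are to be recruited. The two hospitals "are each responsible for 50% of recruitment for the clinical study".

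**The concern.** Comparing the three treatments is a stated aim of the trial. Symptom and quality-of-life scores usually differ between patients before treatment, and part of that difference carries over into the later scores. An ANOVA of final values leaves the carried-over part in the error term. An ANOVA of changes subtracts the whole baseline value, which over-corrects unless the correlation is close to 1. Regressing on the baseline removes the part that the data support.

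With 30 patients per arm required, the loss could decide whether a moderate difference between arms is seen. It also leaves chance baseline differences between arms unadjusted, or over-adjusted, in the estimate. The article commits to a named method that fits its own data collection poorly, so this is a question of the choice made and not of missing detail.

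**Working it through.** **The plan's own figure.** 90 × (1 + 0.20) = 108, which reproduces the stated recruitment. (Dividing instead, 90 / 0.80 = 112.5, gives 113; and 108 × 0.80 = 86.4, about 29 per arm.) The 90 cannot be re-derived, because the article gives no effect size, SD or power. The illustration below uses the required 90 / 3 = 30 per arm.

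**Inputs.**
- From the article: 30 per arm, P < 0.05, and a baseline for every outcome.
- Assumed: a two-sided test, equal SD σ at baseline and at the later visit, and a correlation ρ between them of 0.3, 0.5 or 0.7. The article gives no correlation, so the range is shown throughout.

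**Residual variance of the three analyses.**
- ANOVA of final values: σ²
- ANOVA of changes: σ² + σ² − 2ρσ² = 2(1 − ρ)σ²
- Baseline-adjusted (ANCOVA): (1 − ρ²)σ²

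ANCOVA is not less precise than either, apart from one degree of freedom. Against final values the gain is ρ². Against changes the difference is 2(1 − ρ) − (1 − ρ²) = (1 − ρ)², which is never negative.

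| ρ | Final values | Changes | ANCOVA | Cut against final values | Cut against changes |
|---|---|---|---|---|---|
| 0.3 | 1 | 1.40 | 0.91 | 9% | 1 − 0.91/1.40 = 35% |
| 0.5 | 1 | 1.00 | 0.75 | 25% | 1 − 0.75/1.00 = 25% |
| 0.7 | 1 | 0.60 | 0.51 | 49% | 1 − 0.51/0.60 = 15% |

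**In patients.** Thirty per arm with ANCOVA carry the information of 30/0.91 = 33, 30/0.75 = 40 and 30/0.51 = 59 per arm under ANOVA of final values. At ρ = 0.5, 1/0.75 = 1.33, so either ANOVA needs 33% more patients.

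**In power.** Take the pairwise difference that gives 80% power with ANOVA of final values at 30 per arm: (1.960 + 0.842) × √(2/30) = 0.723 SD. For the same difference:

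| ρ | Final values | Changes | ANCOVA |
|---|---|---|---|
| 0.3 | 80.0% | 65.8% | 83.6% |
| 0.5 | 80.0% | 80.0% | 89.9% |
| 0.7 | 80.0% | 95.1% | 97.5% |

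**Hospital term.** If hospital explains an assumed 1%, 5% or 10% of outcome variance, adding it moves power from 80% to 80.4%, 82.0% or 84.0%. It costs almost nothing and adds little; most of the gain comes from the baseline.

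**The case against.** The strongest reply is that a journal article abbreviates. One sentence naming ANOVA does not rule out covariates or a repeated-measures form, and a fuller plan may supply them. ANOVA after randomisation is also valid: without differential drop-out it estimates the arm differences without bias. The size of the loss rests on assumed correlations, and at 0.3 the gain over final values is only 9% of variance. The entry rule of a mean VAS of at least 4 narrows the baseline range, which may push the VAS correlation towards the low end. The trial also describes itself as exploratory.

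Much of this stands, and it limits the point to precision and to a lower severity. It does not remove the point. The article says what baseline data are for and does not list adjustment of the arm comparison, and both readings of the ANOVA lose precision.

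Four stronger readings are tempting, and the document does not support them:
- **Drop-outs are discarded and the analysis relies on completers.** An ANOVA at one visit would by default omit patients without that visit, and inflating 90 for drop-out fits such an analysis. But the article states no analysis set and no missing-data rule.
- **The ANOVA is one-way and ignores the baseline, or is repeated in each of 12 weeks.** The form, the use of final values or changes, and the time points are all unstated. An ANOVA of changes would use the baseline, only less efficiently.
- **The randomisation table is not divided by hospital.** The article says that "selected cases will be distributed in a 1:1:1 ratio to generate a randomized grouping table" and is silent on stratification. With recruitment split equally, a list per hospital is just as compatible with that text.
- **The markers must be analysed on the log scale.** The article gives no marker distributions, so nothing in it supports that prescription.

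**Conclusion.** The point holds as a should-fix. The stated between-arm method names no baseline covariate, although every outcome has a baseline, and it is less precise than baseline adjustment whether it is applied to final values or to changes. For ρ between 0.3 and 0.7 the avoidable residual variance is 9% to 49% of that of a final-value ANOVA, and 35% down to 15% of that of a change-score ANOVA. These sizes depend on the assumed correlations and on equal SDs at the two visits. The direction does not depend on which correlation in that range applies.

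The harm is lost precision, not bias. A hospital term is worth including but contributes little. The extra benefit of a mixed model over ANCOVA lies in using the scores of patients who leave early. It depends on how many leave and when, and it is not quantified here.

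**What to change.** Replace the ANOVA sentence by a baseline-adjusted comparison of the three randomised arms: an ANCOVA with arm, baseline value of the same outcome and hospital, at the end of treatment (week 8) and the end of follow-up (week 12). This applies to VAS, RQLQ and the five blood markers, all of which are already measured at those times.

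For VAS and RQLQ, preferably fit it as a mixed model for repeated measures on the weekly scores, with arm, week, arm-by-week, baseline, baseline-by-week and hospital, and read the arm contrasts at weeks 8 and 12. Patients who leave early then contribute the scores they gave, on the assumption that missing scores are missing at random given the data in the model. If a simpler analysis is preferred, ANCOVA at the two named visits recovers the gain calculated above.

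The trial is listed as ongoing. The cost is a change of wording, which should be made before the data are analysed, and slightly more analysis work. No new data or patients are needed.

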**Methods/design:**

This randomized controlled trial aims to study the impact of acupuncture on the HPA axis of patients with moderate and severe AR. This research also aims to compare the curative effects of different treatments in three groups of patients: those receiving western medicine, western medicine and conventional acupuncture, or western medicine and mind-regulating acupuncture. We will study the therapeutic effect of acupuncture and the correlation between the changes of therapeutic indexes and experimental indexes after the treatments. Therapeutic indexes include the Visual Analog Scale (VAS) of nasal symptoms and the Rhinoconjunctivitis Quality of Life Questionnaire (RQLQ) for AR patients; experimental indexes include corticotropin releasing hormone (CRH), adreno-corticotropic hormone (ACTH), cortisol (CORT), interleukin 4 (IL-4), and interferon-γ (IFN-γ).

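### The stated between-arm ANOVA includes no baseline adjustment although all five hormone and cytokine markers are measured at baseline; ANCOVA, on the log scale if skew is seen, would gain power at almost no cost

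*Protocol article*

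**What the plan says.** The Outcomes section lists the laboratory measures: "The experimental indexes are serum CRH, plasma ACTH, cortisol, serum IL-4, and IFN-γ". They are sampled at baseline, at the end of treatment and 4 weeks later; the Recruitment section also requires the pre-treatment blood test.

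For continuous data the Statistical analysis section offers three things:

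- a summary: "The main and second indexes of therapeutic effects will be measured as mean ± standard deviation"
- a within-arm test: "Differences before and after the treatment in each group will be compared by paired" t-test
- a between-arm test: "ANOVA will be used in the comparison between groups"

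No covariate, normality condition or transformation is attached. The one alternative test stands in a separate sentence: "Count data will be measured by constituent ratio while chi-square test or non-parametric test will be used in the comparison between groups". The significance rule is P "<0.05 indicates the difference is statistically significant".

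The five markers are not named in that section. The abstract defines the other class of outcome: "Therapeutic indexes include the Visual Analog Scale (VAS) of nasal symptoms and the Rhinoconjunctivitis Quality of Life Questionnaire (RQLQ) for AR patients". The markers form a second class, the experimental indexes.

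**The concern.** The five markers carry the trial's declared purpose, which is the effect of acupuncture on the HPA axis. The trial plans for about 30 evaluable participants per arm, so there is little power to spare. A one-way ANOVA on follow-up values leaves between-person variation in the error term, and the baseline sample could remove part of it. The paired t-tests do use baseline, but only inside each arm, so they do not compare treatments.

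The scale of analysis is a second and lesser matter. If marker concentrations are clearly right-skewed, a few high values inflate the raw-scale error variance. As written, the non-parametric option does not reach continuous outcomes. At stake is the chance of detecting a real difference between arms, and the width of the intervals around it.

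**Working it through.** **Inputs from the protocol.** Three arms, allocated 1:1:1; "the required sample size is 90; taking into account a 20% drop-out rate, a total of 108 cases will be recruited". So 90/3 = 30 evaluable per arm, and 108 = 90 × 1.2. (If 20% of 108 drop out, 108 × 0.8 = 86.4 remain, about 29 per arm, which is close enough to 30 here.) Alpha is 0.05. No effect size, SD or power is given for any marker, so the plan has no power figure of its own to reproduce.

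**Inputs assumed.** Log-normal markers; geometric-mean ratios 1/0.80/0.65; baseline-to-follow-up correlation ρ = 0.5 on the log scale; log-SD 0.4 to 0.8.

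**Step 1: baseline adjustment alone.** Take the error variance of ANOVA on follow-up values as 1. With equal variances, ANOVA on change has 2(1 − ρ) and ANCOVA has 1 − ρ².

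| ρ | Change | ANCOVA |
|---|---|---|
| 0.3 | 1.40 | 0.91 |
| 0.5 | 1.00 | 0.75 |
| 0.7 | 0.60 | 0.51 |

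Since 2(1 − ρ) − (1 − ρ²) = (1 − ρ)² ≥ 0, ANCOVA does at least as well as change, and it beats follow-up alone whenever ρ ≠ 0, apart from one lost degree of freedom. At ρ = 0.5 intervals shorten by 1 − √0.75 = 13%.

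**Step 2: closed-form power on the log scale, log-SD 0.6.** The log means are 0, −0.2231 and −0.4308, with mean −0.2180 and sum of squared deviations 0.09283.

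- ANOVA: λ = 30 × 0.09283/0.6² = 7.736; noncentral F(2, 87) gives power of about 69%.
- ANCOVA: λ = 7.736/0.75 = 10.31; noncentral F(2, 86) gives about 81%.

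**Step 3: simulation, including the raw scale.** At least 3,000 replicates per cell, so the error is about 1 point.

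| Log-SD | Raw ANOVA, follow-up | Raw ANOVA, change | Log ANOVA | Raw ANCOVA | Log ANCOVA |
|---|---|---|---|---|---|
| 0.4 | 95% | 87% | 97% | 98% | 99% |
| 0.6 | 60% | 47% | 68% | 71% | 80% |
| 0.8 | 33% | 24% | 43% | 40% | 55% |

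The log-scale entries at 0.6 agree with Step 2 within simulation error.

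**Step 4: what the gain is made of (log-SD 0.6).** The total is 80 − 60 = 20 points. Taking scale first: 68 − 60 = 8 from the log, then 80 − 68 = 12 from baseline. Taking baseline first: 71 − 60 = 11 from baseline, then 80 − 71 = 9 from the log. In either order, baseline adjustment supplies more than half.

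**Step 5: scale alone, over a wider range of skew.** One arm is shifted so that log-scale ANOVA has 80% power with 30 per arm. Raw ANOVA power, when that arm is lowered/raised, is:

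- log-SD 0.3: 77%/79%
- log-SD 0.5: 72%/76%
- log-SD 0.7: 65%/73%
- log-SD 1.0: 51%/63%

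Kruskal-Wallis stays at 77–78% throughout.

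**Step 6: false positives.** With no true difference, raw ANOVA rejects in about 4–5% of trials under the Step 3 settings, and in 3.5% at log-SD 1.2 under the Step 5 settings. The rate is nominal or conservative.

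**The case against.** The strongest reply is that this is a condensed article. Normality checks, transformations, fallback tests, rank-based sensitivity analyses and rules for values below the assay limit commonly sit in an analysis plan that is not shown. That stands, and none of those is raised here as an omission.

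A reader might also infer that the markers will be analysed on the raw scale. The text does not say so. It neither names the markers nor rules out a transformation, and its mean ± SD sentence is limited to therapeutic indexes. ANOVA can be run on logged values. What remains is that ANOVA is the only between-arm test stated for continuous data: either it covers the markers, or they have no stated comparison.

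Skew is not shown either. The documents contain no marker data, and with mild skew the scale hardly matters (Step 5, log-SD 0.3).

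Finally, the ANOVA might be meant for changes, since the abstract speaks of changes in both kinds of index. That would use baseline, but less efficiently than ANCOVA (Step 1), and under the Step 3 settings it has lower power than follow-up values alone.

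**Conclusion.** The point holds as a choice of method. An unadjusted ANOVA is stated, the baseline values are collected anyway, and ANCOVA is the more efficient comparison. Under the assumed inputs, power at log-SD 0.6 rises from about 60% (raw ANOVA) to 71% (raw ANCOVA) and 80% (log ANCOVA). At log-SD 0.4 or below the gain in power is small, partly because power for the assumed effect is already near its ceiling; the gain in precision from the covariate remains.

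The case for the log scale depends on skew that the documents do not show. The case for the baseline covariate needs only a non-trivial correlation between baseline and follow-up.

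A reader might infer that raw-scale ANOVA could produce spurious differences between arms. Step 6 does not support this: the harm is lost power and precision. Because the protocol calls the study exploratory and sets no power target for any marker, severity is low.

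**What to change.** In the Statistical analysis section, replace the between-arm ANOVA for the five experimental indexes with ANCOVA across the three randomised arms: end-of-treatment value as outcome, arm as factor, baseline value of the same marker as covariate. State that outcome and covariate are log-transformed if the sponsor's preliminary study or blinded pooled data show right skew, and that this choice is fixed before unblinding. On the log scale, report geometric-mean ratios with 95% confidence intervals.

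The cost is one or two sentences. No new data are needed, and the named software (SPSS 21) can fit the model. The drawback is that log-scale results read as ratios and not as differences in concentration.

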## Discussion

AR has become a global and intractable disease. Besides negative impacts on patients’ quality of life, it results in various kinds of diseases which may cause the loss of working ability and life. Although the symptoms can be relieved effectively by various topical or oral drugs, susceptibility to the disease cannot be changed. Specific immunotherapy can relieve the allergic symptoms, but long-term treatment always results in poor compliance [16]. Acupuncture, on behalf of traditional treatments, reflects the emphasis of TCM on “mind-regulation”. In all kinds of diseases, especially physical and mental disorders, treatments which emphasize both a patient’s physiological and mental state, play an important role. Recent research proves that [17] AR is a physical and mental disorder, being closely related to social psychological factors. AR patients, especially those with moderate and severe disease, are likely to have mental and behavior problems due to the chronic and unstable symptoms, continuous and unsuccessful treatments, accumulated medical expenses, and effects on their social function. Furthermore, a patient’s mental and behavior problems may aggravate their illness [18]. As a result, a vicious cycle is formed.

In 2001, WHO organized a discussion, attended by Otolaryngology experts from around the world, on the impact of AR on asthma and the concept of “one airway, one disease” has been proposed. Except for differences in their clinical symptoms, AR and asthma are similar in various aspects, such as pathogenic and pathological changes [19]. At present, the HPA axis has become the focus in research on the mechanisms involved in AS [20]. Some scholars feel that the HPA axis of AR patients is likely to be activated. After stimulation of patients’ nasal cavities by allergens, the detection of ACTH and cortisol in the peripheral blood circulation indicates that AR can activate the HPA axis [21]. However, by considering the complexity of the pathogenic mechanism of AR, the influence of chronic, long-term, repeated stimulation of the HPA axis of patients with moderate or severe persistent AR is unclear.

On the basis of a large number of references and related research, a hypothesis is suggested that patients with moderate or severe persistent AR undergo a long-term change in stress status both physically and mentally. High stimulation activates the HPA axis continuously, with excessive secretion of hormones resulting in selective inhibition of Th1 cells. The balance tends to move towards the humoral immune system mediated by Th2 and this increases patients’ susceptibility. On the other hand, long-term activation of the HPA axis may induce HPA axis exhaustion and lead to its dysfunction, resulting in lost control and limitation of the allergic inflammation. This may be one of the reasons for AR recurrence. Acupuncture can relieve patients’ nasal symptoms and modulate their psychological state by regulating hormones and cytokines of the HPA axis. This moderates the functions of the NEI system to relieve the allergic inflammation of AR. However, this RCT is an exploratory study with limited experience. Therefore, the sample size, outcome evaluation items, and follow-up pattern should be improved in the future.

